### Health economics analyses

Outcomes will be assessed using the primary trial outcome and the EQ-5D-5 L. The primary analysis will be undertaken at 12 months from an National Health Service and Personal Social Services perspective. A broader perspective including patient’s personal expenditures will be included in a sensitivity analysis. Incremental cost effectiveness ratios will be computed by comparing the costs and outcomes of both arms of the trial. The difference in effectiveness will be expressed in terms of the change in score on the primary outcome measure (cost-effectiveness analysis). The difference in utility will be expressed in terms of quality adjusted life years calculated using patient reported EQ-5D 5 L data. This will be used in a cost utility analysis to calculate the incremental cost per quality adjusted life years gained.

### Missing data

For missing data (participant withdrawal or interim missing data), the plausibility of missing data models ‘missing at random’, ‘missing completely at random’, ‘missing not at random’ will be ranked by the trial personnel (informed by the available trial data). The most plausible missing data model will be selected and a sensitivity analysis will be conducted accordingly to explore the effect of departures from assumptions made in the primary analysis. Upon completion of sensitivity analyses, an appropriate method of missing data imputation will be selected.

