### Sample size

In the absence of availability of detailed information on the clinical meaningful difference in outcome measured using the FFI pain subscale, the calculation of our desired effect size was based upon previous findings from an FOs trial for people with RA [52]. This trial evaluated 6 month FFI pain subscale scores at 6 months following intervention with either a functional FO versus a non-functional placebo-type flat FO. Mean difference at 6-month outcome (9.93) and pooled standard deviation (19.77) values were obtained from this study to calculate a standardised mean difference. For a two-tailed hypothesis, to detect a standardised mean difference of 0.5 (9.93/19.77) (a medium to large effect size) at 0.05 significance, 0.8 power and 20% attrition (based on the randomised controlled trials by Woodburn et al. [30]), we require 160 participants (80 per arm) [Statistics Calculators, 2015].

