### Analysis

Data will be analysed according to the intention-to-treat principle. Data will be explored to determine whether or not potential confounders need to be accounted for in the final analysis. Should we detect any imbalances between intervention groups, we expect that the analysis of the primary outcome (FFI pain subscale) will be conducted using an analysis of covariance (ANCOVA) with adjustment for relevant baseline values and potential confounders. For example, to account for systemic disease activity as a covariate, the FFI pain subscale change scores will be adjusted according to both FFI pain subscale baseline scores and the change scores of the Disease Activity Scale for 28 joints between baseline and follow up. Statistical methods for secondary/additional analyses: Similarly, for comparison of all other secondary outcomes, between group scores from baseline to 12 months will be compared using ANCOVA with adjustment for baseline values and potential confounders. All estimates for primary and secondary outcomes will be reported with estimated effect sizes alongside 95% confidence intervals.

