## Discussion

FOs have been used clinically for many decades for the treatment of foot pain in patients with RA, although their effectiveness has not been rigorously evaluated as a management method. Despite this, foot care recommendations feature in many United Kingdom and European clinical guidelines. However, the level of supporting evidence is low, mainly at ‘good clinical practice’ and ‘expert opinion’ agreement level [26]. This could be due to various reasons: the numerous types of FOs available in the market place; the variation of prescription habits between clinicians; and the biomechanical effects of the FOs on the lower limb, which we believe to be clinically beneficial are limited throughout the literature [59]. Further, customised orthoses commonly follow the ‘subtalar joint neutral theory’ for foot morphology even when criticised for its reliability and validity [60]. Three reviews investigating the effect of FOs in RA patients report a general consensus that FOs are beneficial [61–63], yet no insight is given into prescription guidelines or treatment recommendations.

This trial protocol has been designed to provide robust results on orthotic treatment and guidelines in an RA cohort. This is a randomised trial which includes concealed allocation using a web based system, blinding of outcome assessors, blinded data analysis and the use of outcome measures with proven reliability and validity in pain, satisfaction, disease activity and functional limitation. Further, all podiatrists will be trained and provided with prescription protocols (Figs. 2 and 3) to follow ensuring similar prescriptions between the 6 recruitment sites.

This trial aims to provide clinically relevant and robust evidence in regards to clinical outcomes, patient satisfaction and cost-effectiveness. Each of the research questions that will be investigated in this study will provide National Health Services with further knowledge about the use of FOs in this selected patient cohort. Clinical effectiveness evaluation will provide evidence for the National Health Service to practice around the highest standards as well as being aware of patient satisfaction. We anticipate that this project will provide vital evidence and thus guidance to inform clinical decision making in future.

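### Missing data: the imputation method is chosen only after the sensitivity analyses are complete, and no primary missing-data assumption is fixed beforehand

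*Protocol article*

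**What the plan says.** The Missing data section of the protocol article sets out three steps in order.

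1. The plausibility of MAR, MCAR and MNAR "will be ranked by the trial personnel (informed by the available trial data").
2. "The most plausible missing data model will be selected and a sensitivity analysis will be conducted accordingly". Its stated purpose is "to explore the effect of departures from assumptions made in the primary analysis".
3. "Upon completion of sensitivity analyses, an appropriate method of missing data imputation will be selected".

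The Analysis section gives the principle ("Data will be analysed according to the intention-to-treat principle") and a conditional model ("Should we detect any imbalances between intervention groups, we expect that the analysis of the primary outcome (FFI pain subscale) will be conducted using" ANCOVA). It names no missing-data assumption or method. The Sample size section plans "at 0.05 significance, 0.8 power and 20% attrition". The Discussion lists "blinding of outcome assessors, blinded data analysis and the use of outcome measures" among the design's strengths, without saying what the blinding of the analysis covers.

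**The concern.** A completed sensitivity analysis is a set of results. A method of imputation selected after it can therefore be selected with those results in view, and nothing in the article places the decision before database lock or unblinding.

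The order is also circular. Step 2 is meant to examine departures from the primary analysis's assumptions, but the article never says what that analysis assumes about missing scores, and the imputation method is settled only in step 3. The sensitivity analysis has no fixed point to depart from.

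Step 1 does not supply that point. Observed data can count against MCAR, but they cannot tell MAR from MNAR without assumptions that cannot be tested. A ranking informed by the data leaves the distinction that matters most to judgement.

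At stake is the error rate of the 12-month comparison of FFI pain, and how far a reader can trust that the reported handling of dropouts was not picked for its answer.

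**Working it through.** **The plan's own figure.** Inputs from the Sample size section: difference 9.93, SD 19.77, two-sided alpha 0.05, power 0.80, attrition 20%.

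- Normal approximation: n per arm = 2 × (1.960 + 0.842)² × (19.77/9.93)² = 2 × 7.85 × 3.96 = 62.2, so 63. The exact two-sample t-test gives 63.2, so 64.
- Inflation for attrition: 64/0.80 = 80 per arm, 160 in total. The plan's figure reproduces.
- Scores exposed to the choice of method: 0.20 × 160 = 32, or 16 per arm.

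**How far handling can move the estimate.** If missing scores in one arm are shifted by δ points relative to MAR, the estimated difference moves by 0.20 × δ. For δ of 5 to 20 points this is 1 to 4 points, against a target of 9.93.

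**Illustration of choosing after the fact.** These assumptions are not in the documents: no true effect; 80 per arm; correlations 0.5 (baseline to 6 months), 0.5 (baseline to 12 months) and 0.65 (6 to 12 months); 20% MCAR at 12 months, half of those also missing 6 months; baseline-adjusted ANCOVA. The worst case is that any method giving p < 0.05 is the one picked. Results come from simulation runs of 1,500 to 4,000 null trials.

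| Freedom allowed | Type I error |
|---|---|
| One fixed method (complete case, last value carried forward, baseline carried forward, or MAR multiple imputation) | about 0.05 |
| Complete case or MAR imputation | about 0.06 |
| Any of the four | about 0.075-0.08 |
| The four, plus MNAR shifts of ±0.5 SD applied equally to both arms | about 0.08-0.09 |
| The four, plus MNAR shifts of ±0.5 SD in one arm alone | about 0.19 |

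Monte Carlo error for a rate of 0.075 in 4,000 trials is √(0.075 × 0.925/4,000) = 0.004, so run-to-run differences such as 0.074 against 0.078 carry no meaning.

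**Where the 0.19 comes from.** It can be checked by hand.

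- Standard error with 64 evaluable per arm and baseline correlation 0.5: 19.77 × √(1 − 0.25) × √(2/64) = 19.77 × 0.866 × 0.177 = 3.03.
- One-arm shift of 0.5 SD: 0.20 × 0.5 × 19.77 = 1.98 points, or 1.98/3.03 = 0.65 standard errors.
- One such shift used alone: P(Z > 1.31) + P(Z < −2.61) = 0.095 + 0.005 = 0.10 (simulated 0.086 to 0.104).
- Either direction allowed: 2 × 0.095 = 0.19.

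So nearly all of the 0.19 comes from one-arm shifts. Each of them is already biased when data are truly MCAR. The figure therefore does not measure selection among methods that are each valid on their own.

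**The case against.** Several points on the other side are fair.

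- **The imputed result may not be the primary result.** A reader might infer that the selected imputation becomes the primary analysis. The article does not say so. Its reference to assumptions made in the primary analysis suggests that such an analysis already exists, in which case the imputation could be supportive. This stands as a limit on the claim. It does not remove the problem, because the primary assumption is named nowhere and the role of the imputed analysis is left open.
- **The ranking is not baseless.** One might say it has no empirical footing. That goes too far: the text describes judgement informed by data, and the data can speak against MCAR. What they cannot do is separate MAR from MNAR.
- **A primary analysis is described.** To say that none could be interpreted would also go too far. The endpoint, the intention-to-treat principle and a conditional ANCOVA are all given.
- **The error rates are a worst case.** The article names no carried-forward or shifted method, and nothing in it suggests that anyone would pick a result for its p-value. The figures show what the latitude permits; they do not predict what will happen.
- **Blinded data analysis is mentioned.** Masked arm labels would make directional choices harder, above all one-arm shifts. But the phrase is not tied to this decision, and masked labels do not hide effect sizes or p-values.
- **Detail belongs in a SAP.** The imputation model, the variables and the shifts may well be left there, and their absence is no fault. The fault is in what the article does state: an order of decisions that a SAP naming its method in advance would have to depart from.

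**Conclusion.** The Missing data section is wrong as written. It places selection of the imputation method after the sensitivity analyses, following a ranking informed by trial data, with no primary missing-data assumption fixed first. This leaves room for the handling of about 32 of 160 primary scores to be chosen with results in view, and it makes the sensitivity analysis circular.

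Under the assumptions above, the plausible size is modest: type I error of about 0.06 with two standard choices and about 0.075-0.08 with four. The tempting headline of 0.19 holds only if one arm's missing scores may be shifted by half an SD in either direction, and should not be quoted without that condition. The documents show latitude. They do not show intent, nor an error rate that is already inflated.

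**What to change.** Delete the last sentence of the Missing data section and put a fixed order in its place, settled before unblinding:

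1. **Primary method.** One method under MAR: either a likelihood-based repeated-measures model, or multiple imputation using baseline and 6-month FFI pain. Table 1 shows both measurements are already collected.
2. **Sensitivity analyses.** Delta-adjusted MNAR imputation over a stated range, applied to each arm separately and to both. State that these are supportive and cannot replace the primary result.
3. **Ranking.** If kept, it may guide only which sensitivity analyses are emphasised, and should rest on clinical grounds or pooled blinded data.

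The cost is revised wording here and in any SAP, plus minor programming. No new data are needed, the sample size stays at 160, and the primary test is no longer open to choice after results are seen.

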### Ethical consideration

Ethical approval for this study has been obtained by the East of England – Essex Research Ethics Committee Ref: 15/EE/0410. Registration of this RCT has been completed with the ISRCTN registry: ISRCTN31652.

## Discussion

FOs have been used clinically for many decades for the treatment of foot pain in patients with RA, although their effectiveness has not been rigorously evaluated as a management method. Despite this, foot care recommendations feature in many United Kingdom and European clinical guidelines. However, the level of supporting evidence is low, mainly at ‘good clinical practice’ and ‘expert opinion’ agreement level [26]. This could be due to various reasons: the numerous types of FOs available in the market place; the variation of prescription habits between clinicians; and the biomechanical effects of the FOs on the lower limb, which we believe to be clinically beneficial are limited throughout the literature [59]. Further, customised orthoses commonly follow the ‘subtalar joint neutral theory’ for foot morphology even when criticised for its reliability and validity [60]. Three reviews investigating the effect of FOs in RA patients report a general consensus that FOs are beneficial [61–63], yet no insight is given into prescription guidelines or treatment recommendations.

This trial protocol has been designed to provide robust results on orthotic treatment and guidelines in an RA cohort. This is a randomised trial which includes concealed allocation using a web based system, blinding of outcome assessors, blinded data analysis and the use of outcome measures with proven reliability and validity in pain, satisfaction, disease activity and functional limitation. Further, all podiatrists will be trained and provided with prescription protocols (Figs. 2 and 3) to follow ensuring similar prescriptions between the 6 recruitment sites.

This trial aims to provide clinically relevant and robust evidence in regards to clinical outcomes, patient satisfaction and cost-effectiveness. Each of the research questions that will be investigated in this study will provide National Health Services with further knowledge about the use of FOs in this selected patient cohort. Clinical effectiveness evaluation will provide evidence for the National Health Service to practice around the highest standards as well as being aware of patient satisfaction. We anticipate that this project will provide vital evidence and thus guidance to inform clinical decision making in future.

## Abbreviations

ACR: American College of Rheumatology
ANCOVA: Analysis of covariance
EULAR: European League Against Rheumatism
FFI: Foot Function Index
FFI_dis_: Foot Function Index for disability
FFI_fl_: Foot Function Index for functional limitation
FFI_pain_: Foot Function Index pain subscale
FIS: Foot Impact Scale
FIS_RA_: Foot Impact Scale for Rheumatoid Arthritis
FO: Foot Orthoses
HAQ: Health Assessment Questionnaire
HRQoL: Health Related Quality of Life
RA: Rheumatoid Arthritis
RADAI-F5: Rheumatoid Arthritis foot Disease Activity Index
RCT: Randomised Controlled Trial
